## Abstract

**Background:**

Behavioural problems are common in nursing home residents with dementia and they often are burdensome for both residents and nursing staff. In this study, the effectiveness and cost-effectiveness of a new care programme for managing behavioural problems will be evaluated.

**Methods/Design:**

The care programme is based on Dutch national guidelines. It will consist of four steps: detection, analysis, treatment and evaluation. A stepped wedge design will be used. A total of 14 dementia special care units will implement the care programme. The primary outcome is behavioural problems. Secondary outcomes will include quality of life, prescription rate of antipsychotics, use of physical restraints and workload and job satisfaction of nursing staff. The effect of the care programme will be estimated using multilevel linear regression analysis. An economic evaluation from a societal perspective will also be carried out.

**Discussion:**

The care programme is expected to be cost-effective and effective in decreasing behavioural problems, workload of nursing staff and in increasing quality of life of residents.

**Trial registration:**

The Netherlands National Trial Register (NTR). Trial number: NTR 2141

## Background

Many nursing home (NH) residents with dementia suffer from behavioural problems (BPs) like aggression, apathy and agitation. In a recent Dutch study, BPs were present in 80 percent of the residents [1]. BPs are associated with high costs, diminished quality of life of residents and a high workload for nurses [1-3].

Antipsychotics and physical restraints are frequently used to treat BPs [4,5]. However, the use of antipsychotics may have serious negative side effects like extrapyramidal symptoms and increased risk of stroke [6-8] and the use of restraints may result in decreased functional status and quality of life [9].

Various studies have shown that treatments with less adverse effects can be used to manage BPs as an alternative to antipsychotics and physical restraints. For example, Cohen-Mansfield and colleagues [10] observed a positive effect of individualized psychosocial interventions, such as pain treatment, electronic massagers and individualized music. Furthermore, Livingston et al. found in their review that staff education and psychological and psychosocial treatments were effective [11]. Davison et al. [12] also found a significant decrease in BPs through the use of psychosocial interventions in people with dementia in whom individualised pharmacological treatment failed to work.

In line with these studies, recent professional dementia guidelines emphasise the use of a systematic multidisciplinary approach to treat BPs and stress the importance of psychosocial interventions and staff training [13-16]. They also underline that the use of antipsychotics should be restricted as much as possible. Although these guidelines have been developed in collaboration with long-term care professionals, implementation in actual practice is difficult. Unfortunately, this is also the case in Dutch NHs [17], although the presence of various care disciplines offers excellent conditions for a multidisciplinary approach.

A key problem in implementation of guidelines on BPs seems to be that guidelines do not include a structured, methodology-based approach how to manage BPs [18]. For example, an implementation plan on how different disciplines should work together in managing BPs, is often lacking. Therefore, we developed a care programme entitled: 'Grip on challenging behaviour'. This care-programme, which offers a comprehensible structure of the care processes, is made practically applicable and ready to implement. It is based on the guidelines, fits with daily practice, and describes how new working methods are related to and can be integrated in the present care process following a step-by-step plan.

This paper describes the design of the study that evaluates the effectiveness and cost-effectiveness of this care programme for managing BPs in NH residents with dementia.

## Methods/Design

### Aim

The aim of this project is to evaluate the effectiveness and cost-effectiveness of a multidisciplinary care programme for managing BPs in NH residents with dementia. The care programme proposes an evidence- and practice-based standardisation of all consecutive steps in the management of BP: detection, analysis, treatment and evaluation (see figure 1). Cooperation between disciplines is also prearranged and structured.

**Figure 1 F1:**
[figure not shown]
**Components of the care programme 'Grip**** on challenging behaviour'**.

### Intervention

In the first step, the care programme offers a screening tool to detect symptoms of BPs, next to the usual (daily) observation and detection of BPs by nurses. When (symptoms of) BPs are detected, structured forms are used to analyse the behaviour in the next step of the care programme. The nursing staff starts the analysis, after which the elderly care physician and the psychologist continue analysis when necessary. The outcome of the analysis is discussed in pre-arranged multidisciplinary team meetings in which the members of the multidisciplinary team choose the treatment option (or options) they consider appropriate, resulting in a written treatment plan (third step). Psychosocial interventions are first line treatment options and psychotropics or physical restraints should only be used when psychosocial interventions have no or not enough effect. In the fourth step, treatment is evaluated. Standard scales are used for rating BPs when evaluating the effect of interventions. When treatment outcomes are unsatisfactory, alternative treatment options may be chosen and/or a new analysis will be done.

### Design

The care programme will be implemented using a stepped wedge design (Table 1). A stepped wedge design is a type of cross-over design in which different clusters (in this case dementia special care units (SCUs)) cross-over from control-condition to intervention over time [19]. In this study, fourteen participating units are randomly divided over five groups. Four groups consist of three dementia SCUs from three different NHs, one group consists of two dementia SCUs from two different NHs.

**Table 1 T1:** Flow chart of the stepped wedge design (0 = control condition; 1 = intervention).

	T0	T1	T2	T3	T4	T5
Group 1	0	1	1	1	1	1
Group 2	0	0	1	1	1	1
Group 3	0	0	0	1	1	1
Group 4	0	0	0	0	1	1
Group 5	0	0	0	0	0	1

The groups will start with the care programme on six different point in time (T0 through T5)

Six measurement cycles will take place: one measurement cycle every four months during a period of twenty months. The first measurement cycle is a baseline measurement on all participating units. After each measurement cycle, except the last one, a new group will start the intervention. The moment after which measurement cycle a group of units will start is randomised.

A process analysis will be carried out during the study on the actual provision and use of the components of the care programme and on barriers and facilitators of implementation. The process analysis will consist of qualitative interviews with key persons within the NHs.

### Sampling

We calculated the sample-size using the following assumptions: On average, a dementia SCU houses 20 residents. Based on a previous study, we expect that 5% of the residents' (legal) representatives will not give informed consent [1]. We expect no further attrition, because newly admitted residents will replace discharged and deceased residents during the study. For the primary outcome, we assume that our care programme leads to a 10 point decrease of BPs, measured with the Cohen-Mansfield Agitation Inventory (CMAI)[20]. Based on a Dutch study in NH patients [21], we assume a mean Intra Class Correlation Coefficient of 0.1. for clustering of BPs within a unit and a mean score of 47.7 (SD = 16.6) on the CMAI in NH patients with dementia.

Based on these assumptions and a significance level (alpha) of 0.05 and a power (beta) of 0.80, 14 dementia SCUs with 6 measurements are needed in a stepped wedge design.

The participating dementia SCUs will be recruited from NHs that collaborate with the VU University Medical Center (Amsterdam) and the Radboud University Nijmegen, Medical Center. The dementia SCUs participating in this study are not allowed to exchange staff between SCUs, in order to avoid carry-over effects, and thus dilution of the effect.

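### The stated need for 14 units does not follow from the protocol's own inputs: with an immediate full effect, this stepped wedge has over 99% power for 10 CMAI points and 80% power for about 4

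*Protocol article*

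**What the plan says.** The Sampling section of the protocol article gives a full set of planning inputs:

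- Unit size: "On average, a dementia SCU houses 20 residents", and "we expect that 5% of the residents' (legal) representatives will not give informed consent". No further attrition is expected, because new admissions replace residents who leave or die.
- Effect: "we assume that our care programme leads to a 10 point decrease of BPs" on the CMAI.
- Variability: "a mean score of 47.7 (SD = 16.6) on the CMAI in NH patients with dementia".
- Clustering: "we assume a mean Intra Class Correlation Coefficient of 0.1. for clustering of BPs within a unit".
- Error rates: "a significance level (alpha) of 0.05 and a power (beta) of 0.80".

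From these it concludes that "14 dementia SCUs with 6 measurements are needed in a stepped wedge design". The Design section and Table 1 fix the layout: "Six measurement cycles will take place: one measurement cycle every four months during a period of twenty months", with five groups of 3, 3, 3, 3 and 2 units, one group crossing over after each cycle except the last. The article names no sample-size formula. It gives no within-resident correlation, no between-period correlation, no delay in effect and no safety margin.

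**The concern.** A stepped wedge with six measurements on every unit compares each unit with itself as well as with the others. At an ICC of 0.1 and about 19 residents per unit, that should need far fewer units than a single-measurement comparison of two arms. The Discussion itself credits the design with increasing power. Yet 14 units is what such a two-arm comparison would need, so no gain from the design shows in the number.

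What is at stake is how the result is read. If 14 units really gave 80% power at 10 points, a significant result would point to an effect of at least several points. If the design is much more precise than stated, significance can occur at a small fraction of the planning effect, and the Sampling section would not tell the reader so.

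**Working it through.** **Inputs.** From Sampling: 20 × 0.95 = 19 residents per unit per cycle; difference 10; SD 16.6, so variance 275.56; ICC 0.1; alpha 0.05 (taken as two-sided, since sidedness is not stated); power 0.80. From Design and Table 1: five sequences, six measurements, 3/3/3/3/2 units. Which group has two units is not stated; it is placed last here, and other positions move the 80%-power difference only between 3.84 and 3.90 points.

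**Step 1: which calculation returns 14?** Take a parallel cluster trial with one measurement.

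- Unclustered n per arm = 2 × (1.96 + 0.8416)² × (16.6/10)² = 43.26.
- Design effect = 1 + (19 − 1) × 0.1 = 2.8.
- 43.26 × 2.8 = 121.1 residents per arm; 121.1 / 19 = 6.37 units per arm, rounded up to 7, so 14 in total.
- Power is 83.5% with 7 per arm and 77.6% with 6. Using 20 residents per unit also gives 7 per arm.

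The match relies on the normal approximation. With a t reference, 7 per arm gives about 77% power, and 16 units would be needed.

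**Step 2: the stepped wedge as described.** The model is linear with a random unit effect constant over time, fixed period effects and independent residuals (Hussey and Hughes).

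- Between-unit variance τ² = 0.1 × 275.56 = 27.56.
- Variance of a unit-period mean within unit σ² = 0.9 × 275.56 / 19 = 13.05.
- From Table 1, with I = 14 units and T = 6 periods: U (intervention unit-periods) = 15 + 12 + 9 + 6 + 2 = 44; W (sum of squared period totals) = 0 + 9 + 36 + 81 + 144 + 196 = 466; V (sum of squared unit totals) = 75 + 48 + 27 + 12 + 2 = 164.
- Var = Iσ²(σ² + Tτ²) / [(IU − W)σ² + (U² + ITU − TW − IV)τ²].
- IU − W = 616 − 466 = 150; U² + ITU − TW − IV = 1936 + 3696 − 2796 − 2296 = 540.
- Var = 14 × 13.05 × 178.39 / (150 × 13.05 + 540 × 27.56) = 1.936, so SE = 1.391.

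Results: 80% power at 2.8016 × 1.391 = 3.90 points (3.80 with 20 residents per unit); significance at an estimate of 1.96 × 1.391 = 2.7 points; power for 10 points above 99.99%.

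**Step 3: assumptions the article does not state** (19 residents per unit, normal reference).

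| Correlation structure (assumed) | 80% power at (points) | Power for 10 points |
|---|---|---|
| Same residents throughout, within-resident correlation 0.5 | 2.8 | >99.9% |
| Same, 0.8 | 1.8 | >99.9% |
| Cluster autocorrelation 0.8 | 4.6 | >99.9% |
| Cluster autocorrelation 0.5 | 5.3 | >99.9% |
| Decaying correlation 0.8 | 5.0 | >99.9% |
| Decaying correlation 0.5 | 5.7 | 99.8% |

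With a t reference on 12 degrees of freedom, the last row falls to 99.4%. An ICC anywhere from 0.01 to 0.3 keeps the 80%-power difference at 3.5 to 3.9 points. To bring 14 units down to about 80% power for 10 points would take 2 to 3 residents per unit per cycle (73% at 2, 87% at 3), against the 20 stated.

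**Step 4: gradual onset** (also an assumption; same model, analysed as on/off).

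- Half the effect at the first cycle after start, full from then on: a 10-point eventual effect is estimated as 5.9 points, and the eventual effect detectable with 80% power is 6.6.
- One third, two thirds, then full: it is estimated as 3.2 points, power is about 64%, and the detectable eventual effect is about 12 points.

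**The case against.** **Gradual onset.** This is the strongest reply. The programme runs through detection, analysis, treatment and evaluation, and cycles are four months apart, so the effect may well build up. Step 4 shows that power for a 10-point eventual effect can then fall well below 99%, even below 80%. This stands as a condition on any restated power figure. It does not rescue the stated number, because the article gives no lag among its assumptions and Table 1 codes the intervention as fully on from the first measurement after start.

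**Small consequence.** On the stated inputs the trial is larger than its target requires. No enrolment, design or analysis decision changes. This also stands and limits the weight of the point.

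**Stronger readings the documents do not support:**

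- A reader might infer that the authors used a parallel-trial formula. The numerical match is exact under the normal approximation, but the article names no formula and says the calculation is for a stepped wedge. The match may be coincidence.
- A reader might infer that a handful of units would do. One unit in each of the five groups gives 99% power only with a normal reference; a t reference on 3 degrees of freedom gives about 81%. That is no basis for a smaller trial.
- A reader might infer that a significant result will be misread as a 10-point effect. The article neither calls 10 points a minimal important difference nor says that significance alone decides the interpretation. The risk is that the paragraph invites such a reading, not that the plan commits to it.

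**Conclusion.** The point holds in a limited form. The claim that 14 units are needed for 80% power at 10 points in this stepped wedge is not reproduced by the stated inputs. With period effects, a constant unit effect and an immediate full effect, 14 units give over 99% power for 10 points and 80% power for about 4 points. Across the correlation structures tried, the latter figure ranges from about 2 to 6 points, and power for 10 points stays above 99%. These figures assume a two-sided test and the full effect from the first measurement after start; gradual build-up would lower them.

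On those terms the error is conservative and does not leave the trial underpowered. Its practical size is that an estimate near 2.7 points, about a quarter of the planning effect, would already be significant in the base case. The labelling of power as beta is a separate slip with no effect on the figures.

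**What to change.** Keep 14 units and rewrite the closing statement of the sample-size calculation. Name the formula used and the within-resident and between-period correlations assumed, or say that none were. Suggested wording:

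*With 14 units of about 19 residents and six cycles, analysed with period effects, ICC 0.1 and assuming the full effect from the first measurement after start, the trial has 80% power for a CMAI difference of about 4 points (about 2 to 6 under other correlation structures) and over 99% for 10 points; a gradual build-up of effect would lower this.*

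If the authors' calculation rested on an assumption not printed, such as a delayed effect, they should state it and give its figures instead. Add that the result will be interpreted by its estimate and confidence interval against the 10-point planning effect. Write power as 1 − beta = 0.80.

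The cost is one reworded paragraph, with no change to enrolment, design or data collection.

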### Ethical approval

The study protocol was approved by the Medical Ethics Review Committee of the VU University Medical Center. All data will be anonymized and (legal) representatives will have the opportunity to object to the use of data from their relative.

### Measurements

#### Patient characteristics

*Sociodemographic variables *(e.g., age, gender, and length of stay) and the use of physical restraints will be collected from resident charts.

*Severity of dementia *will be determined by elderly care physicians, using the Global Deterioration scale (GDS) [22]. The GDS is a validated seven-point scale that describes seven different stages of dementia ranging from "subjectively and objectively normal" to "severe dementia".

*Data about psychotropic drug use (including antipsychotics) *will be derived from the NH pharmacists' electronic registration system and will be classified according to the Anatomical Therapeutic Chemical (ATC) classification system [23].

*Behavioural problems *will be measured using the Cohen-Mansfield Agitation Inventory (CMAI) and the Neuropsychiatric Inventory - Nursing Home version (NPI-NH). To our knowledge, the CMAI is the only instrument specifically addressing agitation and aggression, with an adequate validity and reliability for the Dutch version [24,25]. The CMAI will be used in primary effect analyses that focus on agitation and aggression, which are the most prevalent and most stressing BPs [4].

The NPI-NH is a version of the Neuropsychiatric Inventory [26] that is adjusted to the NH setting. The questionnaire contains twelve items which each measure the frequency and severity of a neuropsychiatric symptom. It was developed for rating by professional caregivers within institutions [27,28]. The Dutch version proved to be valid and reliable [29].

*Quality of life *of residents will be measured with the Qualidem, a Dutch dementia specific observational quality of life instrument. With this instrument, nursing staff can rate quality of life of the resident over the last week. The Qualidem has nine subscales: Care relationship, Positive affect, Negative effect, Restless tense behaviour, Positive self image, Social relations, Social isolation, Feeling at home and Having something to do. The Qualidem was proven to be valid and reliable, although some items are not applicable to patients with severe dementia (GDS state 7) [30,31].

#### Nursing staff characteristics

Characteristics of the nursing staff (e.g. gender, working experience) are collected through the use of a questionnaire.

Workload of nursing staff will be assessed using the Dutch version of the Maslach Burnout Inventory [32], the Utrechtse Burnout Scale-C [33]. The UBOS measures three components of workload and burnout: emotional exhaustion, depersonalisation and decreased personal accomplishment.

Job satisfaction will be measured using two subscales of the Leiden quality of work questionnaire [34]. The two subscales measure job satisfaction and work and time pressure. The attitude of nursing staff to dementia care will be measured using the approaches to dementia questionnaire (ADQ) [35].

#### Special dementia care unit characteristics

The Special Care Unit Environmental Quality Scale (SCUEQS) is used for the characteristics of the physical environment. The SCUEQS is a summary scale comprised of items from a larger observational instrument (the TESS-NH) which gathers data on the physical environment of a long-term care facility. The eighteen items measure maintenance, cleanliness, safety, lighting, physical appearance/homelikeness, orientation/cuing and noise [36]. In addition information about nursing staff-resident ratio and educational level of nursing staff will be gathered.

### Data analysis

The CMAI-score and the NPI-NH score will be used as a primary outcome. Age, gender, length of stay, dementia severity, prescription of antipsychotics and of other psychotropics will be used as covariates. For the primary and secondary outcome analyses, multilevel linear regression and multilevel logistic regression analyses will be used. These analyses will calculate effects on neuropsychiatric symptoms, quality of life (Qualidem), prescription rate of antipsychotics, workload and job satisfaction of nursing staff and use of physical restraints.

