## Discussion

The aim of this study is to measure the effectiveness and cost-effectiveness of an evidence- and practice-based care programme for managing BPs in NH residents with dementia. Primary outcome is the effect on prevalence of BP. Secondary outcomes are the effect on quality of life, use of antipsychotics and physical restraints and on workload and job satisfaction of nursing staff. Additionally, an economic evaluation will be carried out.

We assume that implementation of the care programme will result in a decrease of BPs and, subsequently, in an increase of the quality of life of the residents. We also expect lower costs that will most likely be the result of a decrease of behavioural-problem related extra care, a decrease of medication, fewer admissions to hospital and also by a lower absence rate of nursing staff. Implementation is also expected to result in a lower workload and higher job satisfaction among nursing staff.

The chosen design to implement and evaluate the care programme is suitable for our purposes. Not only does the stepped wedge design increase the power of the study by enabling between-groups and within-group analyses, it also ensures that implementation of the care programme occurs in all participating care units, which likely increases motivation for participating in the study [40]. Except for the EQ5D, which is used to calculate QALYs, the chosen outcome parameters are all commonly used in the field of nursing home medicine and are also suitable for the population of severely demented patients [22,24,27,31].

The study has some limitations that should be mentioned. One limitation of the study is that, although data collection will be done by research assistants who are blinded for the trial condition, the NH staff will be aware of receiving the intervention, which may cause bias. To limit this bias, nursing staff will not be informed about the scores on the outcome measures. Another limitation is that we use proxy measures only, which may not be as reliable as patient measures [41]. However, in advancing stages of dementia, cognition and communication decrease, which makes the use of proxy measures inevitable [41]. Nevertheless, the described care programme for managing BP in NH residents with dementia and the chosen stepped wedge design seem very appropriate for our research goals.

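### The primary outcome is named inconsistently: the CMAI in the sample size, the CMAI and NPI-NH scores in the analysis section, and prevalence of behavioural problems in the Discussion

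*Protocol article*

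**What the plan says.** The protocol article describes the primary outcome in five places.

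- **Abstract, Methods/Design:** "The primary outcome is behavioural problems". No instrument is named. The same paragraph says that the programme effect will be estimated by multilevel linear regression.
- **Sampling:** "For the primary outcome, we assume that our care programme leads to a 10 point decrease of BPs", measured with the CMAI. The planning values are "a mean score of 47.7 (SD = 16.6) on the CMAI in NH patients with dementia" and an intraclass correlation of 0.1, with "a significance level (alpha) of 0.05 and a power (beta) of 0.80". Nothing comparable is given for any other instrument.
- **Measurements, Patient characteristics:** the CMAI and the NPI-NH are both listed as measures of behavioural problems, but only one is tied to the primary analysis: "The CMAI will be used in primary effect analyses that focus on agitation and aggression".
- **Data analysis:** "The CMAI-score and the NPI-NH score will be used as a primary outcome". For primary and secondary outcomes together, "multilevel linear regression and multilevel logistic regression analyses will be used", with no statement of which model goes with which outcome.
- **Discussion:** "Primary outcome is the effect on prevalence of BP". No instrument or cut-off is given.

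**The concern.** These statements differ in two ways. The first is the number of instruments: one in Sampling and Patient characteristics, two in Data analysis. The second is the type of quantity: a mean score in Sampling and Data analysis, a proportion in the Discussion. The instruments also cover different ground. The CMAI addresses agitation and aggression, while the NPI-NH covers twelve neuropsychiatric symptoms.

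The primary outcome decides what counts as a positive trial. With two scores called primary and no rule for combining them, a reader cannot tell whether the 0.05 in the sample-size section is the error rate for the trial's main claim or only for one of two routes to it. A reader also cannot tell whether the stated power refers to that claim. Two features that the Discussion itself lists as limitations make a clearly fixed primary outcome more important: nursing home staff know when they receive the programme, and all measures are proxy ratings.

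**Working it through.** **Inputs.** From Sampling: alpha 0.05, power 0.80, difference 10 CMAI points, SD 16.6, intraclass correlation 0.1, 20 residents per unit less 5% non-consent = 19, and 14 units. Assumed here: two-sided tests (the article does not state sidedness) and the correlation between the CMAI and NPI-NH test statistics (not given, so shown over a range).

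**Step 1: what the stated figures cover.** Every planning input belongs to the CMAI. The 14 units can be reached with a parallel cluster-trial calculation:

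- Residents per arm before clustering: 2 × (1.96 + 0.84)² × 16.6² / 10² ≈ 43.2, rounded up to 44.
- Design effect: 1 + (19 − 1) × 0.1 = 2.8.
- 44 × 2.8 = 123.2 residents per arm; 123.2 / 19 ≈ 6.5, so 7 units per arm and 14 in total.

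A stepped-wedge (Hussey–Hughes) calculation with the same inputs gives a standard error of about 1.39 points and power above 99.9% for 10 points, so 14 is not what that formula requires. That is a separate matter and does not affect this point. By either route the calculation concerns the CMAI score, not the NPI-NH and not a prevalence.

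**Step 2: one primary outcome.** The chance of a false claim is 1 − 0.95 = 0.05, as stated.

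**Step 3: two primary scores, either one sufficient.** For independent tests the familywise error is 1 − 0.95² = 0.0975. For correlated test statistics it is 1 − P(|Z₁| < 1.96 and |Z₂| < 1.96), here from 2 million simulated bivariate normal draws:

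| Assumed correlation | Familywise error |
|---|---|
| 0 (exact) | 9.75% |
| 0.3 | 9.5% |
| 0.5 | 9.1% |
| 0.7 | 8.4% |
| 0.9 | 7.0% |

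Every value in the range exceeds 5%.

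**Step 4: two primary scores, both required.** The chance that both are falsely significant cannot exceed 0.05, so there is no inflation. The power to meet this requirement cannot exceed the smaller of the two separate powers. The NPI-NH power cannot be calculated, because the article gives no effect or SD for it.

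**Step 5: score or prevalence.** Sampling plans a mean decrease in points, Data analysis names scores, and the Abstract names linear regression. Only the Discussion speaks of prevalence. The logistic model in Data analysis does not show that a binary primary outcome is planned, since antipsychotic prescription and physical restraint use, in the same paragraph, call for one.

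**The case against.** The strongest defence is that the passages can largely be read together. The Abstract names one construct, behavioural problems. Patient characteristics says that two instruments measure it and gives the CMAI the part concerned with agitation and aggression. Data analysis then names both instruments. Sizing a trial on one of two primary measures is not in itself a contradiction. On this view only the term prevalence is out of place, and it is a slip: the next paragraph of the Discussion speaks simply of a decrease in behavioural problems.

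Part of this stands. Prevalence is probably loose wording. How multiplicity is handled may also properly sit in an analysis plan that is not shown, so the absence of an adjustment method from a condensed article is not a finding.

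The defence does not remove the rest. Sampling attaches the primary outcome to the CMAI alone, and Data analysis gives the NPI-NH equal standing. Whether there are one or two primary outcomes is something this article itself states, in two ways.

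A reader might go further and infer three competing primary tests with no error control, an error rate of 1 − 0.95³ = 14.3%, and freedom to choose the winner after seeing the data. The article does not support that. No section plans three primary tests. Independence would be implausible for a prevalence derived from the same kind of behavioural ratings. The trial registration and the ethically approved study protocol, neither of which is shown, may fix the outcome.

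**Conclusion.** The point holds as an inconsistency in naming the primary outcome, with a conditional consequence for error control. Sampling and Patient characteristics point to the CMAI, Data analysis adds the NPI-NH without a success rule, and the Discussion uses a term for a different type of outcome.

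The size depends on a rule that the article does not give. If either score suffices, the 0.05 becomes 9.75% at most and about 7.0% even at a correlation of 0.9; these figures assume two-sided tests at 0.05 each, and the correlations are assumptions. If both scores are required, the error rate is intact but the stated power does not describe the trial's claim. It would therefore be wrong to say that the 0.05 fails; it may not hold. No intention to select an outcome is shown. The inconsistency should be settled because it concerns what the trial sets out to demonstrate.

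**What to change.** - **Data analysis:** name the CMAI total score, analysed as continuous in the multilevel linear model, as the single primary outcome. Make the NPI-NH score the first secondary outcome.
- **Discussion:** replace the reference to prevalence with the CMAI score.
- **Abstract:** name the CMAI as the measure of the primary outcome.

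This follows the sponsor's own sample-size basis. If the sponsor prefers to keep both scores as primary, Data analysis should state one of two rules: both must be significant at 0.05, or the NPI-NH is tested at 0.05 only if the CMAI is significant. Either keeps the familywise error at or below 0.05. The both-required rule would also need planning values for the NPI-NH before any power could be claimed.

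The cost is wording in three places. The NPI-NH loses independent primary status. Design, data collection, number of units and power for the CMAI are unchanged.
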